### Objectives

1.3

The primary objective of this study is to evaluate the proportionate reduction in the occurrence of severe RIOM, as assessed using RTOG grading scale, among participants receiving a Siddha regimen as an adjunct to standard care compared with those receiving standard care alone, assessed during radiotherapy and at six weeks post-radiotherapy.

The secondary objectives are to assess the proportionate reduction in the severity of radiation-induced oral mucositis using WHO oral mucositis scale at the same time points; to compare oral cavity pain intensity between the study groups using VAS, assessed weekly throughout the study period; to evaluate changes in analgesic usage, including escalation or de-escalation according to the WHO Three-Step Analgesic Ladder, on a weekly basis during the study period; to estimate and compare the proportion of adverse reactions between the study groups; and to evaluate differences in the frequency and duration of treatment interruptions attributable to oral mucositis between the study groups.

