### Trial design

2.2

This study is designed as a superiority, phase II, randomised controlled, open-label, two-arm parallel-group trial comparing participants with RIOM receiving a Siddha regimen as an adjunct to SOC with those receiving SOC alone. The primary endpoint of the study is the reduction in the incidence of severe RIOM, which will be assessed using RTOG grading scale during the course of radiotherapy and again at six weeks after completion of treatment. Participants will be randomly assigned in a 1:1 ratio (Siddha + SOC Vs SOC alone) using variable block sizes to maintain balance between groups, and allocation concealment will be ensured through the sequentially numbered, opaque, sealed envelope (SNOSE) technique. Subgroup analyses are also planned according to treatment modality, including radiotherapy alone, concurrent chemoradiotherapy, and post-operative radiotherapy. Since the study is designed as an open-label trial, centralised assessment of outcomes will be performed wherever possible to reduce the risk of assessment bias.

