### Outcomes

2.5

The primary outcome of the study is the severity of RIOM, assessed using RTOG grading scale. This will be measured as the proportion of participants who develop severe oral mucositis (RTOG grade ≥ 3) at any time during radiotherapy and up to six weeks following completion of radiotherapy, compared between the two study arms. The primary outcome will be assessed from randomisation until the last day of study medication use.

The secondary outcomes include oral mucositis severity assessed using WHO oral mucositis scale, measured as the proportionate reduction in the occurrence and severity of mucositis during radiotherapy and up to six weeks post-radiotherapy. Oral cavity pain, evaluated using VAS as the proportion of participants achieving a minimum two-point reduction in pain intensity and analgesic usage, assessed as the percentage of participants requiring analgesics categorised according to WHO three-step analgesic ladder. Safety outcomes will be evaluated by documenting the number of adverse events reported in each study group. Treatment interruption will be assessed as the proportion of participants experiencing one or more radiotherapy interruptions due to severe RIOM and the total number of days of missed radiotherapy. In addition, body weight changes during radiotherapy, requirement for nasogastric tube feeding, and interruptions in oral intake will be documented as exploratory indicators of nutritional impact. All secondary outcomes, except treatment interruption, will be assessed from randomisation until the last day of study medication use, while treatment interruption will be evaluated until the completion of radiotherapy.

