### Statistical methods

4.5

Baseline demographic and clinical characteristics of the participants will be summarised using descriptive statistical methods. Categorical data will be presented as frequencies and percentages, whereas continuous data will be expressed either as mean ± standard deviation or as median with interquartile range, based on the distribution of the data.

The primary outcome of the study, namely the severity of oral mucositis assessed using RTOG and WHO oral mucositis scales, will be analysed by comparing the proportion of participants who develop grade ≥2 mucositis in the two study groups. Depending on the suitability of the data, either the chi-square test or Fisher's exact test will be used for comparison. In addition, weekly mucositis grade distributions will be analysed to observe changes in severity, recovery patterns, and overall trends during treatment and follow-up.

For secondary outcomes, pain intensity measured using VAS will be compared between the groups at each assessment point using either the independent samples t-test or the Mann–Whitney U test, based on the data distribution. Analgesic use, categorised according to WHO three-step analgesic ladder, will be analysed as categorical data and compared between groups using the chi-square test or Fisher's exact test. Rescue medication use will be analyzed as a secondary outcome to compare overall analgesic requirements between the study groups. Laboratory investigations will be summarised descriptively and assessed for safety through appropriate within-group and between-group analyses.

The distribution of continuous variables will be checked using histograms to determine normality. Depending on the nature of the data, either parametric or non-parametric statistical methods will be applied for between-group comparisons. Subgroup analyses based on cancer treatment modalities will also be carried out to explore whether the treatment effects remain consistent across clinically relevant subgroups. However, these analyses will be considered exploratory in nature.

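### The primary outcome is RTOG grade ≥3 in section 2.5, but section 4.5 tests grade ≥2 on RTOG and WHO, and no test of RTOG grade ≥3 is stated

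*Protocol article*

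**What the plan says.** Three sections of the protocol article point to severe mucositis on the RTOG scale.

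- Section 1.3 (Objectives): the primary objective is to "evaluate the proportionate reduction in the occurrence of severe RIOM, as assessed using RTOG grading scale".
- Section 2.2 (Trial design): "The primary endpoint of the study is the reduction in the incidence of severe RIOM", to be assessed on RTOG.
- Section 2.5 (Outcomes): the measure is "the proportion of participants who develop severe oral mucositis (RTOG grade ≥ 3) at any time during radiotherapy" and up to six weeks after it ends. Of these three, only this section gives a grade.

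Section 2.5 also fixes the place of the other scale: "The secondary outcomes include oral mucositis severity assessed using WHO oral mucositis scale". Section 2.7 (Sample size) starts from a 43.6% rate of severe mucositis on benzydamine.

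Section 4.5 (Statistical methods) describes something else. It introduces "The primary outcome of the study, namely the severity of oral mucositis assessed using RTOG and WHO oral mucositis scales" and says that this outcome "will be analysed by comparing the proportion of participants who develop grade ≥2 mucositis in the two study groups", by a chi-square or Fisher's exact test. It adds that weekly grade distributions will be examined for trends.

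**The concern.** The primary analysis has to test the primary outcome. Here the two descriptions differ in threshold (≥3 against ≥2) and in scale (RTOG alone against RTOG and WHO). Table 3 shows that the thresholds describe different states: RTOG grade 2 is patchy mucositis or moderate pain, and grade 3 is confluent mucositis or pain that needs narcotics.

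Two things are at stake. First, a trial that follows section 4.5 would not test the effect it was set up to find, and its result could not carry the claim about severe mucositis that the Conclusion hopes to make. Second, while two thresholds and two scales stand side by side in an open-label trial that is already enrolling and plans interim analyses (section 5.1), the choice of which result counts as primary stays open.

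**Working it through.** **1. The two descriptions side by side**

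| Element | Section 2.5 | Section 4.5 |
|---|---|---|
| Scale | RTOG (WHO is secondary) | RTOG and WHO |
| Threshold | Grade ≥3 | Grade ≥2 |
| Combining rule | Not needed | None given |
| Between-arm test | None stated | Chi-square or Fisher's exact |

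No section calls grade ≥2 severe or presents it as a sensitivity analysis. The weekly grade distributions in sections 4.1 and 4.5 are not a test of the proportion who ever reach RTOG grade ≥3. If WHO were part of the primary analysis, patients whose WHO grade is recorded as not applicable because of tube feeding (section 4.1) would also need a rule.

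**2. What the section 4.5 test cannot see**

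For a patient's worst grade, P(≥2) = P(2) + P(≥3). If the regimen lowers P(≥3) by d by holding those patients at grade 2, P(2) rises by d and P(≥2) does not change. The test then rejects only at its nominal rate of about 5%, however large d is.

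**3. Which rate the sample size rests on**

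The formula printed in section 2.7 is m = (Z₁₋α + Z₁₋β)² [πS(1−πS) + πT(1−πT)] / (πT − πS − δ)².

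- πS = 0.436; πT = 0.85 × 0.436 = 0.3706; δ = 0.15.
- (1.645 + 0.842)² = 6.183, using the one-sided 5% Z and 80% power.
- Variance term: 0.2459 + 0.2333 = 0.4792.
- Denominator: (−0.0654 − 0.15)² = 0.0464.
- m = 6.183 × 0.4792 / 0.0464 = 63.8, so 64 per arm; 64 / 0.8 = 80 after dropout.

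The plan's figure is reproduced. It needs the one-sided Z (the stated two-sided 5% gives 81.1) and a margin whose sign enlarges the difference. Two other combinations come close: 78.6% vs 43.6% with δ = 0.15, one-sided, gives 64.0; and 43.6% vs 20.9% (the 52% reduction), two-sided without a margin, gives 62.8. All three use the 43.6% severe rate, and none uses a grade ≥2 rate.

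**4. Power on each endpoint at 64 per arm, two-sided 5%**

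- Severe endpoint, 43.6% vs 37.06%: SE = √(0.4792/64) = 0.0865; 0.0654/0.0865 = 0.756; power = Φ(0.756 − 1.96) + Φ(−0.756 − 1.96) = 0.114 + 0.003, about 12%.
- Grade ≥2 endpoint: the article gives no rate. Assuming a control rate of 80%, 90% or 95% and the same 15% relative reduction, power is about 34%, 53% or 70%.

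**5. Type I error if the scales were two tests**

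With each scale at 0.05 and either able to win, independence gives 1 − 0.95² = 9.75%. With positively correlated scales it is lower but still above 5%. This applies only under that rule, which section 4.5 does not state.

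**The case against.** The contradiction itself has no good answer. It cannot be left to an unseen analysis plan, because the article fixes the grade ≥2 threshold and both scales itself. Section 3.4 provides for assessors unaware of allocation and for analysis by coded groups, which limits biased grading. Coding does not stop a threshold or scale from being picked by its p-value.

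The stronger objections concern what a reader might infer beyond this, and they stand.

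- **That the mismatch costs power.** It does not on these figures. Under the assumed grade ≥2 rates, the section 4.5 endpoint has more power (34% to 70%) than the severe endpoint (about 12%) for the same relative reduction. The harm is that the test answers another question.
- **That most irradiated patients reach grade ≥2.** The article does not say so. Its figures of 90% or more (section 1.1 and the Discussion) are for mucositis of any grade, under concurrent chemoradiotherapy or high-dose treatment, while the trial also covers radiotherapy alone and post-operative radiotherapy.
- **That type I error is inflated.** This holds only if either scale may win. A composite is an equally possible reading.
- **That the sample size was set for RTOG grade ≥3.** Section 2.7 gives neither scale nor grade for the 43.6%, and it applies the 15% reduction to the occurrence of mucositis without the word severe. The link is a reasonable inference, not a statement.

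**Conclusion.** The concern holds as a contradiction between the defined primary outcome and the stated primary analysis, and it must be corrected. It rests on the text alone and needs no assumed rate. As written, the primary test is of grade ≥2 mucositis on two scales with no combining rule. It does not respond to a shift from grade 3 to grade 2, and it could not support a conclusion about severe mucositis.

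The numbers are secondary. The 9.75% is conditional on two independent tests with either able to win. The grade ≥2 power figures depend on rates the article does not give and show no harm from the mismatch. A reader might also infer that restoring RTOG grade ≥3 makes the trial adequately powered. It does not: power is about 12% for 43.6% vs 37.06% at 64 per arm, a separate problem of the sample size calculation.

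**What to change.** In section 4.5, state one primary analysis: the proportion of participants with RTOG grade ≥3 at any time in the section 2.5 window, compared between arms. Label the WHO-scale analyses and any grade ≥2 analysis as secondary, outside the primary test.

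Record the change in a dated amendment, before anyone sees comparative data, including the interim data for the monitoring committee. Section 6.2 requires ethics committee approval of amendments before they are implemented, and enrolment has started, so this should be done promptly.

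The cost is one amendment. No extra data are needed for the change of threshold and scale, because both scales are already collected, and the planned 64 (80 with dropout) per arm does not change through this correction. One related point is not settled by rewording section 4.5: Table 2 schedules no RTOG grading in weeks 9 to 12, although section 2.5 counts events up to six weeks after radiotherapy. The amendment should reconcile the two.

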#### Comparator description

2.4.2

Participants in Arm B will receive SOC alone for the management of RIOM, as described in the intervention arm. Additional topical anaesthetic and anti-inflammatory gels will be provided for oral mucositis of grade ≥ 2 in accordance with institutional protocol.

Assessments will be conducted weekly, in parallel with the intervention arm, until 6week post radiotherapy or until recovery, whichever occurs earlier. Treatment adherence will be monitored by the oral hygiene coordinator, staff nurse, and investigators, with family caregivers trained during the radiotherapy admission period to assist in monitoring during the post-radiotherapy phase. Trial interventions will be administered for 10–13 weeks, depending on the required radiation dose (Gy) based on tumour size and severity. Recovery will be defined as Grade 0 oral mucositis on both RTOG and WHO oral mucositis scales. All participants will receive radiotherapy using a linear accelerator (LINAC) with three-dimensional conformal radiotherapy (3DCRT) for a duration of 4–7 weeks, in accordance with institutional practice. Before initiation of radiotherapy, all participants will undergo a baseline oral examination and receive necessary dental care, wherever feasible, according to institutional standard dental care protocols. Standardized oral hygiene instructions will be provided and reinforced uniformly throughout the study period in both study arms.

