### Participant timeline

2.6

Participants will undergo initial screening and randomisation at baseline, followed by a 14-week observation period comprising weekly clinical evaluations and periodic laboratory assessments as detailed in the timeline below (Table 2).

**Table 2 T2:** Schedule of enrolment, interventions, and assessments.

Activity/Assessment	Baseline	W1	W2	W3	W4	W5	W6	W7	W8	W9	W10	W11	W12	W13
Enrolment														
Screening & Informed Consent	X													
Randomisation & Allocation	X													
Intervention														
Study Intervention	X	X	X	X	X	X	X	X	X	X	X	X	X	X
Efficacy Assessment														
RTOG Scale	X	X	X	X	X	X	X	X	X					X
WHO oral mucositis Scale	X	X	X	X	X	X	X	X	X	X	X	X	X	X
VAS		X	X	X	X	X	X	X	X	X	X	X	X	X
WHO 3-step analgesic ladder		X	X	X	X	X	X	X	X	X	X	X	X	X
Interruption of RT		X	X	X	X	X	X	X	X					
Days of Missed RT		X	X	X	X	X	X	X	X					
Safety & Laboratory Assessment														
Safety Monitoring		X	X	X	X	X	X	X	X	X	X	X	X	X
CBC	X								X					X
LFT	X								X					X
RFT	X								X					X

RT, radiotherapy; RTOG, Radiation Therapy Oncology Group; WHO, World Health Organization; VAS, visual analogue scale; CBC, complete blood count; LFT, liver function test; RFT, renal function Test; W1−13, No. of week.

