Efficacy analysis will follow a modified *intention-to-treat* approach, including all randomised participants who have undergone at least one post-baseline assessment. Safety analysis will be performed using the per-protocol population. A two-sided *p* value of ≤0.05 will be considered statistically significant. All statistical analyses will be carried out by a statistician using the Statistical Package for the Social Sciences (SPSS) software.

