## Conclusion

8

In conclusion, this study is an effort to scientifically evaluate the role of Siddha medicine as an adjunct to contemporary oncology care in the management of RIOM. The study aims to address an important supportive-care need through the use of accessible, affordable, and culturally acceptable interventions. If Siddha regimen is found to be more effective than SOC alone in reducing severe RIOM, pain, and treatment interruptions without causing additional toxicity, it may contribute to improving patient-centred care in head and neck cancer radiotherapy settings. The findings may also help support the development of integrative oncology practices and future national guidelines.

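### VAS pain is tested between arms at each of up to 13 weekly assessments at unadjusted p ≤0.05, and no comparison is named as deciding the pain objective

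*Protocol article*

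**What the plan says.** All references are to the protocol article.

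- **Section 1.3 (Objectives)** makes pain a secondary objective: "to compare oral cavity pain intensity between the study groups using VAS, assessed weekly throughout the study period".
- **Section 2.6, Table 2** has the row "VAS X X X X X X X X X X X X X". That is 13 marks, weeks 1 to 13; the baseline cell is empty.
- **Section 4.5 (Statistical methods)** states that "pain intensity measured using VAS will be compared between the groups at each assessment point using either the independent samples t-test or the Mann–Whitney U", the choice depending on the distribution. The section closes with one general rule: "A two-sided *p* value of ≤0.05 will be considered statistically significant". It names no deciding week, summary measure, longitudinal model, testing order or adjustment for pain. Only the treatment-modality subgroups are called exploratory.
- **Section 2.5 (Outcomes)** defines the pain outcome differently, as pain "evaluated using VAS as the proportion of participants achieving a minimum two-point reduction in pain intensity".
- **Sections 2.4.1 and 2.4.2** end weekly assessment at recovery if that comes before six weeks after radiotherapy. Section 2.4.2 adds: "Trial interventions will be administered for 10–13 weeks".

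**The concern.** Followed as written, the plan produces up to 13 p-values for one secondary objective and calls each one significant if it reaches 0.05. Nothing says which of them answers the question, so a pain difference could be reported from whichever week crosses the line.

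Two features of the trial make this matter more. Pain is scored by the patient in an open-label trial, and the blinded assessors of section 3.4 do not blind the patient's own rating. Assessment also stops at recovery, so as described the later weekly tests compare only participants who have not yet recovered, a group selected after randomisation.

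Section 2.5 might have supplied the missing contrast but does not. A two-point reduction needs a starting value and a visit at which it is judged. Neither is given, no VAS is scheduled at baseline, and section 4.5 contains no test of that proportion. The outcome named is not the outcome analysed.

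**Working it through.** The plan states no error rate for the pain tests, so there is no figure of its own to reproduce.

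**Inputs**
- Number of tests k: 13 (Table 2). For the shortest course k = 10 (4 weeks of radiotherapy + 6 weeks; the longest is 7 + 6 = 13).
- Threshold: two-sided 0.05 per test (section 4.5), i.e. 0.025 in each direction, critical value 1.96.
- Correlation between weekly test statistics: not in the document. It is an assumption, varied from 0 to 0.9.

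**Independent weeks (upper end)**
- Either direction: 1 − 0.95^13 = 0.487.
- Favouring the Siddha arm only: 1 − 0.975^13 = 0.281.
- With k = 10: 1 − 0.95^10 = 0.401 and 1 − 0.975^10 = 0.224.

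**Correlated weeks.** I simulated k correlated standard normal statistics under no true difference (400,000 draws) and counted the draws with any |z| > 1.96, then those with any z > 1.96 in the favourable direction. With equal correlation between all weeks and k = 13:

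| Assumed correlation | Any significant week, either direction | Any week falsely favouring Siddha |
|---|---|---|
| 0 | 48.7% | 28.1% |
| 0.3 | 41.9% | 21.4% |
| 0.5 | 33.3% | 16.7% |
| 0.7 | 24.1% | 12.0% |
| 0.9 | 13.8% | 6.9% |
| Nominal, one test | 5% | 2.5% |

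With correlation that decays between weeks (AR(1), k = 13), the either-direction figure is 43.4% at 0.5, 36.6% at 0.7 and 22.6% at 0.9. The favourable-direction figures are 23.5%, 19.1% and 11.3%. With k = 10 and equal correlation 0.5 they are 28.7% and 14.3%.

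In the favourable direction the inflation is 16.7 / 2.5 = 6.7-fold at correlation 0.5 and 6.9 / 2.5 = 2.8-fold at 0.9. It exceeds nominal in every case tried.

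**What one averaged contrast would do to power.** Assume 64 per arm (the pre-dropout size in section 2.7), complete data, equal correlation 0.5 and a difference of 0.4 SD. The 0.4 SD is my illustration.
- One week: 0.4 × √(64/2) = 2.26, power about 62%.
- Mean of 13 weeks, effect constant: the variance is (1 + 12 × 0.5)/13 = 0.538 of a single week's, so 2.26 / √0.538 = 3.08, power about 87%.
- Mean of 13 weeks, effect present in only 6: 3.08 × 6/13 = 1.42, power about 30%.

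Averaging therefore helps or hurts depending on whether the window covers the weeks in which an effect exists.

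**The case against.** The best defence is that pain is secondary in a phase II trial, that multiplicity rules for secondary outcomes are commonly left to a statistical analysis plan, and that section 2.5 already names a single pain measure. The first part stands and limits the importance of the point. The second does not remove it: this document itself fixes a test at each assessment and the threshold for each, so a later plan with one deciding contrast would have to depart from section 4.5. The third fails because the measure in section 2.5 has no reference visit, no deciding visit and no analysis.

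Several stronger readings are tempting and are not supported:

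- **That a false pain benefit has a 33% chance.** That figure counts both directions and needs an assumed correlation of 0.5. On the same assumption, the figure for a result favouring the Siddha arm is about 17%.
- **That different weeks could show significant effects in opposite directions.** At correlation 0.5 with no true difference, the chance of this is under 0.1%. It reaches about 7% only if weekly scores in the same patients were independent.
- **That a single averaged contrast always gains power.** It does for a constant effect with complete data. Section 1.1 describes mucositis that appears at about 20 Gy and peaks near 66–70 Gy, so a concentrated effect is plausible.
- **That weekly significance tests are also planned for mucositis grades and analgesic steps.** Section 4.5 describes the weekly grades as a look at trends, and states no week-by-week test for the analgesic ladder.
- **That the Conclusion plans a pain claim from one week.** Its wording is conditional and joint: "If Siddha regimen is found to be more effective than SOC alone in reducing severe RIOM, pain, and treatment interruptions without causing additional toxicity".

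**Conclusion.** The concern holds for the secondary pain objective. The plan specifies up to 13 unadjusted tests and no deciding comparison, and the outcome defined in section 2.5 is not the one analysed in section 4.5. The error rate for pain is above nominal in every scenario examined. Its size cannot be fixed from the document, because it depends on a between-week correlation that is not given; the ranges in the table should be quoted rather than any single value. They rest on normal test statistics and on all 13 weeks being tested, and they do not model the selection created by stopping at recovery. The primary comparison of severe mucositis is untouched. The change should be made, but it does not threaten the main conclusion.

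**What to change.** 1. Reconcile sections 2.5 and 4.5 by naming one pain quantity and one between-arm test at two-sided 0.05. One option is the arm difference in weekly VAS averaged over a pre-specified window, from a mixed model for repeated measures with arm, week and their interaction. Keeping the responder proportion is another, if its reference visit, deciding visit and test are stated and a VAS is recorded at the reference visit.
2. Define the window relative to the radiotherapy course, since that lasts 4–7 weeks and the same calendar week falls in different phases for different participants.
3. State how weeks after assessment stops at recovery enter the analysis.
4. Report weekly VAS differences as descriptive estimates with 95% confidence intervals and no significance claim. If weekly claims are wanted instead, a Bonferroni threshold would be 0.05/13 = 0.0038 per test.

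**Cost.** Changing the two sections and fitting one model needs no extra participants; the responder option may add one VAS reading. Enrolment has started, so the change calls for a documented amendment made before comparative data are seen. The downside is real: a difference confined to a few weeks could no longer be declared significant by itself, and an average over all 13 weeks loses power if the effect is concentrated around peak mucositis. The window should be chosen with that in mind.

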### Sample size

2.7

A study by Kazemiana *et al*. reported that among patients with head and neck cancer receiving benzydamine for the management of RIOM, the occurrence of severe RIOM was 43.6%, compared with 78.6% in the placebo group. Based on findings from our previous unpublished study, a 52% reduction in RIOM grade was observed after 48 days of treatment with TPC mouthwash and GV oral application, and a separate study evaluating TPC with povidone–iodine reported an RIOM occurrence of 10%. Drawing on these findings and clinical expertise, it is assumed that the addition of Siddha regimen to SOC would result in a 15% relative reduction in the occurrence of RIOM compared with SOC alone. Accordingly, assuming a 15% superiority margin, a two-sided significance level of 5%, and 80% power, the calculated sample size is 64 participants per arm. Allowing for an anticipated 20% dropout rate, 80 participants per group will be recruited, resulting in a total sample size of 160 participants. The formula to calculate superiority of proportion is given below.$$m=\frac{\left(Z\;1\;-\alpha +Z\;1-\beta )\;2\;[\pi S\;(1-\pi S\;)+\pi T\;(1-\pi T\;)\right]}{(\pi T\;-\pi S\;-\delta )\;2}$$where,
*δ*: Superiority limit of the difference in Proportionsπ T: Proportion in Test Treatmentπ S: Proportion in Standard Treatmentπ T – π S: Expected difference in proportions*α*: Significance level1 – *β*: Power

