### Plans for assessment and data collection

4.1

Potential participants will be screened by trained investigators to ensure compliance with the inclusion and exclusion criteria. Screening will include a review of medical records and current radiotherapy or chemoradiotherapy details to confirm the diagnosis of head and neck cancer. Eligible participants will be informed about the study objectives, procedures, risks, and benefits, and written informed consent will be obtained prior to enrolment. All screening details will be documented in the screening form and case record form (CRF), with reasons recorded for screen failures. Participants meeting eligibility criteria will proceed to baseline assessments, randomisation, and initiation of the allocated intervention.

At the screening or baseline visit, detailed clinical and drug histories will be recorded. Clinical examination will then be performed to assess the oral mucositis severity using the RTOG and WHO Oral Mucositis Scales during baseline visit. Baseline laboratory investigations, including complete blood count (CBC), liver function test (LFT), and renal function test (RFT), will be performed. Participants will then be randomised, and study medications will be dispensed as per group allocation. Follow-up assessments will be conducted weekly by trained assessors throughout the course of radiotherapy, with telephonic follow-up continued up to six weeks post-radiotherapy. The severity of oral mucositis will be assessed using RTOG and WHO oral mucositis scales, pain intensity will be measured using a 10-point VAS, and analgesic use will be documented according to WHO three-step analgesic ladder. Details of the grading criteria for all these four scales are presented in Table 3. However, in certain clinical situations, analgesics, particularly opioids, may be prescribed for cancer-related pain rather than for RIOM. In such cases, the indication for analgesic use may not directly reflect RIOM severity. To address this, all analgesic usage will be documented along with the primary indication, and cases where analgesics are administered for non-RIOM-related pain, will be clearly specified with appropriate justification. All assessors and physicians involved in outcome evaluation will be trained in advance regarding grading scales and assessment procedures.

**Table 3 T3:** Assessment scales used for outcome evaluation.

Assessment Tool	Grade/Scale	Grading Description

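### Section 4.5 does not say that the between-arm comparison carries the laboratory safety inference, although within-arm change over a course of (chemo)radiotherapy cannot show added toxicity

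*Protocol article*

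**What the plan says.** On laboratory data, section 4.5 (Statistical methods) has one sentence: "Laboratory investigations will be summarised descriptively and assessed for safety through appropriate within-group and between-group analyses". Descriptive summary and safety assessment are two separate steps in it, and within-group analysis belongs to the second. No test is named for either kind of analysis, and neither is ranked above the other.

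For continuous variables generally, the same section says that "either parametric or non-parametric statistical methods will be applied for between-group comparisons". Its significance rule is general: a two-sided p "value of ≤0.05 will be considered statistically significant", with no exception for laboratory data.

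The data for a randomised comparison are planned. Section 4.1 states: "Baseline laboratory investigations, including complete blood count (CBC), liver function test (LFT), and renal function test (RFT), will be performed". Table 2 in section 2.6 repeats CBC, LFT and RFT at W8 and W13 and does not limit them to one arm. All participants receive radiotherapy, and section 2.2 shows that treatment differs between them: "Subgroup analyses are also planned according to treatment modality, including radiotherapy alone, concurrent chemoradiotherapy, and post-operative radiotherapy".

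**The concern.** The safety question is comparative. Section 8 ties a favourable conclusion to benefit without extra toxicity, meaning toxicity beyond that seen with SOC alone. Only a contrast between arms answers that.

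A within-arm comparison of follow-up with baseline has a different null hypothesis: no change over time in that arm. Radiotherapy is planned for 4 to 7 weeks, so the interval from baseline to W8 spans the planned course, with chemotherapy for some participants. Blood counts and liver or renal values may move in both arms even if the regimen is inert, and a within-arm p-value cannot separate the two causes.

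Two misreadings then become possible. A significant change in Arm A may be reported as a regimen effect. Or significance in one arm only may be read as toxicity (if Arm A) or protection (if Arm B). Neither is a test of the regimen.

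**Working it through.** **Plan's own figure.** The document gives no figure for the laboratory analysis, so there is none to reproduce. The arm sizes come from section 2.7: "the calculated sample size is 64 participants per arm" and "80 participants per group will be recruited, resulting in a total sample size of 160 participants". The step between them checks: 64 / (1 − 0.20) = 80.

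**Inputs from the plan.** n = 64 or 80 per arm; two-sided alpha 0.05; 1:1 allocation.

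**Assumed inputs.** The same mean shift d in both arms, from 0 to 0.5 SD of the change score; no regimen effect; correlation r between baseline and follow-up of 0.5 to 0.7.

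**Step 1: within-arm significance.** For a two-sided paired t-test, p_w is the probability that a noncentral t variable with n − 1 degrees of freedom and noncentrality d√n exceeds the critical value in absolute size. With n = 64 and d = 0.25 the noncentrality is 0.25 × 8 = 2.0, almost equal to the critical value, so p_w is about one half (exactly 50.4%).

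**Step 2: exactly one arm significant.** The arms are independent, so the probability is 2·p_w·(1 − p_w). For d = 0.25 and n = 64 this is 2 × 0.504 × 0.496 = 0.500. In half of those cases (25.0% of trials) the significant arm is the Siddha arm. The expression cannot exceed 0.5.

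**Step 3: between-arm test.** Two-sample t-test on change, 20,000 simulated trials per cell.

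| Common shift d | n per arm | Each arm significant within group | Exactly one arm significant | Between-arm test significant |
|---|---|---|---|---|
| 0 | 64 | 5.0% | 9.5% | 5.0% |
| 0.1 | 64 | 12.4% | 21.7% | 5.1% |
| 0.25 | 64 | 50.4% | 50.0% | 5.1% |
| 0.4 | 64 | 88.3% | 20.6% | 4.7% |
| 0.5 | 64 | 97.6% | 4.7% | 5.1% |
| 0.2 | 80 | 42.4% | 48.8% | 5.0% |
| 0.25 | 80 | 59.8% | 48.1% | 5.1% |
| 0.5 | 80 | 99.3% | 1.4% | 5.0% |

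These are figures per parameter and time point. Discordance between arms peaks at moderate shifts. At large shifts both arms are significant, and the remaining danger is reading Arm A's change alone as a regimen effect.

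**Step 4: precision from the baseline value.** Relative to a comparison of follow-up values only (variance factor 1), with equal variances at the two times:

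- Change score: 2(1 − r), which is 1.00 at r = 0.5 and 0.60 at r = 0.7.
- ANCOVA: 1 − r², which is 0.75 at r = 0.5 and 0.51 at r = 0.7.

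ANCOVA therefore cuts variance by 25% (r = 0.5) to 49% (r = 0.7) against follow-up only. Against change scores the ratio is 0.75 / 1.00 = 0.75 and 0.51 / 0.60 = 0.85, a cut of 25% and 15%.

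**The case against.** The strongest reply is that the sentence already names the valid analysis. A concurrent SOC arm with the same laboratory schedule is planned, and the between-arm comparison keeps its 5% error rate at every shift tried. This stands, and it rules out the reading that laboratory safety rests on within-group tests alone.

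Second, the misuse is not written down. The section speaks of analyses, names no paired test, and does not propose to contrast a significant arm with a non-significant one. This also stands. A reader might infer that the plan will declare toxicity from discordant within-arm p-values, but the text only leaves room for that.

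Third, the high within-arm rates are not inflated type I error. When values truly shift over time the within-arm null is false, and the rates in the table are power to detect a real change. They mislead only if attributed to the regimen.

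Fourth, a reader might infer that section 4.5 fixes an unadjusted between-arm analysis. It does not. The t-test and Mann–Whitney test are named for VAS pain, and the general wording for continuous variables excludes neither ANCOVA nor change scores. Covariate choice may properly sit in the SAP.

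Fifth, section 2.5 measures safety by adverse events per group and lists no laboratory outcome. Section 5.2 has events graded by CTCAE and relatedness judged by investigators, and section 5.2.1 handles abnormal values participant by participant. None of this depends on group p-values, which limits the consequences.

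What survives is that the article places within-group analysis within safety assessment, under a general p ≤0.05 rule, without saying which analysis decides.

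**Conclusion.** The point holds as a minor correction of wording. Section 4.5 names one analysis that can answer the laboratory safety question and one that cannot, and does not say which carries the inference. With no regimen effect, exactly one arm can be significant in up to about half of trials per parameter. That maximum rests on an assumed common shift of about 0.25 SD of change with 64 per arm; at 0.1 SD the figure is 21.7% and at 0.5 SD it is 4.7%.

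This is a risk of misinterpretation. The documents do not support a claim that the planned between-arm test has an inflated error rate, and no efficacy conclusion depends on the point. The figure of about 5% for that test assumes complete data in the randomised arms. Section 4.5 runs safety in the per-protocol population, which is a separate matter that also bears on this comparison.

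Baseline adjustment is a gain in precision and not a correction of validity. Its size depends on the assumed correlations and on which unadjusted analysis it would replace.

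**What to change.** In section 4.5, or in the SAP if it carries this detail, state that:

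- inference on laboratory safety rests on the between-arm difference at W8 and at W13 for each CBC, LFT and RFT parameter, from ANCOVA adjusted for that parameter's baseline value (on a log or rank scale where the distribution is skewed), reported with a 95% CI;
- within-arm change from baseline is descriptive only, and significance in one arm but not the other is not evidence about the regimen.

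The cost is a few lines of text. Baseline values are already collected, SPSS (the software named in section 4.5) fits ANCOVA, and no participants, visits or samples are added.
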